### Sample size

Based on other studies [30, 40] and our data from the initial acceptability of *TEMPO* [26], it is assumed that 40% of dyads approached will be ineligible, 40% will refuse participation, 15% will not return their baseline survey, and 25% will be lost to follow-up. Accordingly, 260 dyads will need to be approached to reach the target sample size 40 dyads (20 per group) at the 3-month follow-up [41].

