### Pilot outcomes justifying a larger trial

As a pilot is not suitable for hypothesis testing [28], the focus is on pilot outcomes justifying a larger trial. Given the lack of published benchmarks for feasibility and acceptability, we aim to introduce rigor by nominating the following values:
The pilot procedures will be feasible if (a) eight dyads/month are recruited across sites, (b) refusal rate does not exceed 45%, (c) missing data are less than 10% [29], and (d) protocol infringements are amenable to change.*TEMPO* will be acceptable if (a) attrition in the intervention group does not exceed 25% [30, 31], (b) 75% of dyads adhere to the *TEMPO* modules, and (c) high system usability is reported.An appropriate measure of clinical significance for a pilot is the effect size (ES) [CONSORT for pilots [28]]. A clinically (not statistically) meaningful finding is defined as an ES > 0.2 [32] for the primary outcomes (QOL and anxiety) of interest at 3 months post-baseline compared with those in the control group. As a secondary assessment of clinical significance is that 25% of participants improve on the primary outcomes by at the least the Minimal Clinically Important Difference (MCID).

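### The 260 dyads to be approached do not follow from the stated loss rates and the 40-dyad target: the rates give about 175 in sequence, or 314 if both 40% rates are shares of those approached

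*Protocol article*

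**What the plan says.** In the protocol article, Methods, Sample size, the plan draws on other studies and the team's own acceptability data: "it is assumed that 40% of dyads approached will be ineligible, 40% will refuse participation", then "15% will not return their baseline survey" and "25% will be lost to follow-up". From these it concludes: "Accordingly, 260 dyads will need to be approached to reach the target sample size 40 dyads (20 per group) at the 3-month follow-up".

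Only the first rate has a stated base, namely dyads approached. The base of the refusal rate is not given. The order of events can be read from Recruitment procedures and from Allocation and randomization: eligibility is confirmed, eligible dyads are invited to consent, consenting dyads complete the baseline survey, and randomisation follows its submission.

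Two other places bear on the figures. The abstract repeats a goal of 40, though its unit there is participants. Pilot outcomes justifying a larger trial makes it a feasibility condition that the "refusal rate does not exceed 45" per cent, and caps attrition in the intervention group at 25%.

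**The concern.** The opening word of the conclusion presents 260 as the result of the rates before it. A reader who multiplies the rates out does not get 260, so at least one of the printed figures (a rate, the target or the 260) is wrong, or a base has been left unstated.

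The stake is practical. In a feasibility pilot the planned funnel is what a reader sets beside the observed recruitment, refusal and retention. If 260 is taken at face value, the implied overall yield is 40/260 = 15.4%, whereas the stated rates imply 22.95% or 12.75% depending on the base of the refusal rate. A planner who reuses the paragraph for the larger trial would not know which yield was intended.

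**Working it through.** **Inputs** (all from Sample size): ineligible 0.40; refusal 0.40; baseline survey not returned 0.15; lost to follow-up 0.25; target 40 dyads at 3 months; stated number to approach 260.

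**Attempt to reproduce 260.** Number to approach = target / product of the retained fractions.

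1. *Each rate applied to the dyads remaining.* Retained fraction = 0.60 × 0.60 × 0.85 × 0.75 = 0.2295. Required = 40 / 0.2295 = 174.3, so 175. Rounding up at each stage, working back from 40: 40/0.75 → 54; 54/0.85 → 64; 64/0.60 → 107; 107/0.60 → 179.
2. *Ineligible and refusing both taken as shares of all approached.* Retained fraction = (1 − 0.40 − 0.40) × 0.85 × 0.75 = 0.1275. Required = 40 / 0.1275 = 313.7, so 314.
3. *Other treatments that use all four rates:*
   - multiplying by (1 + rate) instead of dividing by (1 − rate), rounding up at each stage: 115
   - sequential, but with 15% and 25% added: 40 / (0.36 × 0.60) = 185.2, so 186
   - refusal and baseline non-return added among the eligible: 40 / (0.60 × 0.45 × 0.75) = 197.5, so 198
   - reading 2 with 15% and 25% also added: 40 / (0.20 × 0.60) = 333.3, so 334

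None of these lies within 3% of 260 (about 252 to 268).

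**What 260 approaches would yield.**

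| Stage | Reading 1 | Reading 2 |
|---|---|---|
| Approached | 260 | 260 |
| Eligible | 260 × 0.60 = 156 | – |
| Consenting | 156 × 0.60 = 93.6 | 260 × 0.20 = 52 |
| Baseline returned, randomised | 93.6 × 0.85 = 79.6 | 52 × 0.85 = 44.2 |
| Followed up at 3 months | 79.6 × 0.75 = 59.7 | 44.2 × 0.75 = 33.2 |

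Against a target of 40, reading 1 is about 50% over and reading 2 about 17% short.

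**Which single change would give 260.** Keeping sequential losses and altering one input:

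- target 60: 60 / 0.2295 = 261.4
- refusal 60%, or ineligibility 60%: 40 / (0.60 × 0.40 × 0.85 × 0.75) = 261.4 (exact solution 59.8%)
- loss to follow-up 50%: 40 / (0.60 × 0.60 × 0.85 × 0.50) = 261.4 (exact solution 49.7%)
- baseline non-return: exact solution 43.0%

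Reading 2 with the 15% left out gives 40 / (0.20 × 0.75) = 266.7, also within 3% of 260. Several different slips therefore fit, and the arithmetic cannot choose between them.

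**The case against.** The case for leaving this alone is that 260 is a workload forecast for a pilot not meant for hypothesis testing. It sets no randomised sample, stopping rule or analysis. The feasibility and acceptability criteria concern monthly recruitment, refusal, missing data, protocol infringements, attrition, module adherence and usability, and none refers to 260. Sample and setting says that recruitment concluded in February 2021, before the article appeared in March 2021, so a correction changes no recruitment decision. The larger trial would be planned from observed rates, which Feasibility data says will be reported with confidence intervals. All of this stands and limits the severity. It does not make the figure right. A silent safety margin is not a convincing explanation either, because the text presents 260 as following from the rates.

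Three stronger readings are tempting, and the document does not support them.

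- *That the plan really expected 60% refusal and so would breach its own 45% limit.* The stated refusal assumption is 40%, which is inside the limit. Sixty per cent is one of several values that would give about 261, and nothing in the text points to it.
- *That the real target was 60 dyads (30 per group).* This fits numerically, but the target is printed as 40 (20 per group), and the abstract repeats 40.
- *That the plan certainly over-recruits.* This holds on the sequential reading. The recruitment text supports that reading, since it is eligible dyads who are invited to consent. But for clinic-based recruitment, interest is established before eligibility is confirmed, and the refusal rate has no stated base. On the other reading 260 is too low.

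**Conclusion.** The point holds. The number to approach does not follow from the four stated rates and the 40-dyad target under any reading tried that uses all of them. On the natural sequential reading the requirement is about 175 (179 with stagewise rounding), so 260 is too high by a factor of 260/174.3 = 1.49. If both 40% rates are shares of those approached, the requirement is 314 and 260 is too low, at about 0.83 of what is needed. The direction of the error therefore depends on a base that the article does not give, and which printed figure is wrong cannot be settled from it.

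The calculation assumes only that the rates and target are as printed and that losses occur in the order in which the article describes the stages. Severity is moderate: a stated recruitment figure needs correcting, while the design, the analysis and the progression criteria are untouched.

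**What to change.** Rewrite the Sample size paragraph as a funnel, giving at each stage the rate, its base and the expected number of dyads: approached, eligible, consenting, baseline returned and randomised, followed up. Then make one of these corrections:

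- if the rates are sequential and the rates and 40-dyad target stand, replace 260 with about 175 (179 if each stage is rounded up);
- if ineligibility and refusal are both shares of those approached and the target stands, replace 260 with 314;
- if 260 was intended, correct the target or the rate that was misprinted, and carry a changed target through to the abstract. If the refusal assumption is what changes, check it against the 45% feasibility limit.

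The cost is one paragraph of text, plus the abstract if the target changes. It needs no additional participants or procedures. As recruitment has closed, the correction can be made as a note to the protocol or in the results report, so that observed rates are compared with a funnel that adds up.

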### Recruitment procedures

#### Clinic-based recruitment

Across participating sites, local research assistants (RAs) are calling patients who have previously consented to being contacted about research to introduce the study using information from the study brochure. If the individual is interested, the RA confirms that both the patient and caregiver are eligible. When possible (due to the current restrictions due to COVID-19), RAs work with clinicians at participating sites to identify potentially eligible individuals. With the clinicians’ permission, RAs approach eligible patients either in person or by telephone following their appointment to introduce the study and arrange a time when the screening checklist can be completed in a confidential manner.

#### Community-based recruitment

Dyads are also recruited through self-referral by inviting relevant community organizations across Canada (e.g., Prostate Cancer Canada) to share the study brochure or information from the study brochure with their members, either by posting the information on their social media platform, website, or by circulating it by email. Individuals who are interested are invited to contact the central RA in Montreal using a toll-free number. The RA then answers questions about the study and, if the individual is interested, proceeds with confirmation of eligibility for both the patient and caregiver.

All eligible dyads are invited to complete an online consent form (each province has its own local version, in accordance with local REB requirements). The online consent form does not require a signature, and completing the fields and clicking the submit button is indicative of consent. The same version of the consent form is provided to patients and caregivers; however, the patients and their caregivers each receive their own copy (sent as a PDF by email after completion online, in an encrypted, password-protected folder). The consent form is included in Supplementary Material S2. Once dyads are consented, they receive a link to complete the baseline questionnaire online.

### Allocation and randomization

Once dyads submit their baseline survey, they are randomized by the project coordinator using a computer-generated randomization schedule that uses random block sizes of 2 or 4, with an allocation ratio of 1:1, stratified by severity of HADS Anxiety subscale. SAS University Edition is used. The stratification uses the highest HADS score in the dyad categorized as “none” (HADS score < 8), “mild” (HADS score 8–10) or “moderate/severe” (HADS score ≥ 11) [42]. To ensure allocation concealment and prevent selection bias, only the study coordinator can enter the unique participant identifier [43] into the randomization schedule, along with date of baseline completion and HADS scores of both dyad members. An automated interface, programed by the study statistician, assigns the study group.

### Intervention and control groups

#### TEMPO intervention

All participants in the intervention are given access to TEMPO and continue to use all other resources offered by their cancer centre, independently of this study. The description of TEMPO follows the TiDier template [44].
*Name:* Tailored, wEb-based, psychosocial and physical activity self-Management PrOgram (*TEMPO*) [45]. *TEMPO* is a 10-week, web-based intervention (https://tempo.truenth.ca/) that complements usual care (see Fig. 1 for a screenshot of the *TEMPO* landing page).*Why: TEMPO* aims to increase dyads’ confidence in using self-management strategies demonstrated to be effective in addressing key psychosocial issues (e.g., dealing with stress, communicating with partner and family) and assist dyads in developing the self-regulatory skills necessary to meet the PA guidelines [46–48].*What:* Dyads are invited to complete five modules: (a) identification of need and priorities, (b) setting goals, (c) tracking progress, (d) strengthening your support system, and (e) maintaining behavior change beyond *TEMPO*. Modules were explicitly designed to focus on specific aspects of the behavior change process and integrate key persuasive technology techniques (e.g., primary task support) [49]. Each module specifies online (e.g., worksheets to set goals) and offline (e.g., practicing chosen self-management skills) activities. Table 1 summarizes the content and self-management skills addressed in each of the five modules.In addition to the modules, *TEMPO* includes a health library, incorporating 49 factsheets based on the most up-to-date evidence on self-management and PA (see Fig. 2 for a screenshot of the *TEMPO* Health Library). The content of the health library integrates content developed earlier by our team [11]. The health library includes eight sections: (a) communicating with your health care team, (b) treatment decision-making, (c) dealing with stress and worry, (d) supporting each other, (e) getting the support you need, (f) wanting to feel more fit and healthy, (g) getting on top of symptoms, and (h) caregiving. Table 2 outlines the specific topics covered in each of the sections respectively. A sample factsheet is included in Supplementary Material S3. *TEMPO* is available both in French and in English.*Who provides: TEMPO* is a self-directed intervention, whereby no external guidance is provided, and all the support to navigate the intervention is included in its design. TEMPO was developed by a multi-disciplinary research team, in close collaboration with community organizations, clinicians, health care managers and end users. All collaborators have experience in improving patients’ and caregivers’ adjustment to cancer.*How:* Participants randomized to TEMPO are sent an email with a brief, illustrated instructional guide on creating a TEMPO account (e.g., registration), and on accessing the modules (e.g., website navigation). They are also invited to schedule a phone call with a RA to review the registration instructions, receive support with account creation, and/or receive assistance with module access as required. Any comments or issues reported by participants relating to registration or access is recorded and shared with the research team.Although patients and caregivers might initiate the modules together, they then can progress at their own speed through the content. Once dyads identify their needs, they use the appropriate factsheets to get ideas for self-management strategies to address these and set their goals accordingly.*When and how much:* Participants are advised to wait approximately 2 weeks in-between each module, to pace their learning; however, based on our initial acceptability study [26], each module becomes immediately available upon completion of the preceding module. In the event that participants are completing the modules at a slower than expected pace (2 weeks per module), a reminder email is sent to check-in and offer additional support. If no response is received, and no additional module completion is observed, a second follow-up email is sent 1 week later.*Modifications:* Following our initial acceptability study [45], new health library content was added to help participants engage in PA during COVID-19-related confinement if outside activities are not deemed feasible. Although we had planned to send dyads pedometers and exercise bands, due to COVID-19, this was not possible. Dyads are encouraged to use their smartphone and other household equipment to support their PA.

**Fig. 1 Fig1:**
[figure not shown]
*TEMPO* landing page. This figure illustrates the content and layout of the *TEMPO* platform. Available from https://tempo.truenth.ca

**Table 1 Tab1:**
[figure not shown]
Overview of the five *TEMPO* Modules

**Fig. 2 Fig2:**
[figure not shown]
*TEMPO* Health Library landing page. This figure illustrates the layout of the *TEMPO* Health Library including the eight categories of factsheets

**Table 2 Tab2:** *TEMPO* Health Library Topics of the 49 Factsheets

Communicating with your health care team (***n*** = 6)	Treatment decision making (***n*** = 6)	Dealing with stress and worry (***n*** = 5)
1. Knowing what to expect after a cancer diagnosis or treatment 2. Asking questions to the health care team 3. Knowing the role of the different health professionals involved 4. Understanding what the health care professionals are telling us 5. Having our main concerns addressed during appointments 6. Telling the health care professionals what is going on	1. Making decisions about treatment 2. We do not have enough options 3. Do not understand enough 4. Telling the health care team which decisions we want 5. Feeling pressured to make decisions 6. Managing stress due to treatment-related delays	1. Feeling tense, anger, or stress 2. Feeling worried or uncertain 3. Feeling sad, down, or isolated 4. Feeling unmotivated or low on energy 5. Feeling overwhelmed
**Supporting each other** **(*****n*** **= 6)**	**Getting the support you need (*****n*** **= 7)**	**Wanting to feel more fit and healthy (*****n*** **= 9)**
1. Helping each other feel better 2. Talking about the hard stuff 3. Dealing with conflict 4. Stressed by the changes in our roles and responsibilities 5. Feeling less connected to each other 6. We are different in how much we want to talk about the situation	1. Knowing where to go for more support^a^ 2. Getting more information about cancer and treatment 3. Asking for help from the right health professionals 4. Needing more help at home 5. Getting emotional support 6. Finding financial help 7. Finding legal help	1. Fitting physical activity into our day 2. Exercising and being physically active safely 3. Wanting to be physically active on a budget 4. Getting ideas about how to get physically active 5. Knowing how much physical activity 6. Becoming or staying motivated to do physical activity 7. Knowing how to use a pedometer 8. Knowing how to do resistance training at home 9. Aerobic exercises at home
**Getting on top of symptoms** **(*****n*** **= 7)**	**Caregiving** **(*****n*** **= 3)**	
1. Pain 2. Fatigue 3. Loss of appetite 4. Diarrhea 5. Incontinence 6. Erectile dysfunction 7. Symptom diary	1. Canadian Cancer Society pages on caregiving 2. Canadian Cancer Society pages on support for caregivers 3. Video testimonial from a caregiver, hosted by the Canadian Cancer Society	

^a^Sample factsheet of “Knowing where to go for more support” is included in Supplementary Material S3. Each factsheet uses a similar format and is similar in length

#### Control group

A wait-list control group is used, whereby dyads do not receive access to *TEMPO* initially, but have access to all the resources available at and referred to by their respective participating cancer treatment centers. These dyads have access to support and information provided by multi-disciplinary teams at their treatment centers. Depending on the center, they may also be referred to supportive resources provided by the Canadian Cancer Society or by TrueNTH Canada (an initiative of Prostate Cancer Canada). In addition, they may be encouraged to use local rehabilitation and support group resources for patients and caregivers. A 3-month follow-up questionnaire captures information on the types of support resources that the dyads had been referred to and used. Once these dyads have completed the follow-up questionnaire, they are sent the login information for *TEMPO.*

### Theoretical frameworks that guided the development of *TEMPO*

*Stress and Coping Framework* [50] assumes that individuals who cope better with cancer challenges experience less anxiety. Active coping generally leads to positive adjustment [51], whereas avoidant coping is linked to higher anxiety [52].*Framework of Dyadic Coping* [53] recognizes the impact of the patient–caregiver relationship on each person’s anxiety, whereby positive dyadic coping (e.g., supportive communication) enhances patients’ and caregivers’ reported outcomes [54].*Self-efficacy theory* [55] posits that people are more likely to engage in activities they feel confident doing, with self-efficacy-enhancing strategies including achievement of behavioral goals, behavior modeling by similar others, and verbal persuasion.

### Blinding

Participants are not blinded to group allocation, as the conditions are described in the consent form. However, they are blinded to specific pilot outcomes, reducing potential response biases [56]. Investigators are blinded to group allocation until the database is locked. The coordinator randomizes dyads and cannot be blinded to group allocation. The RAs recruiting participants do not have access to the randomization schedule or to randomized participants.

### Data collection

Participants complete an eligibility screening checklist (T0) and two questionnaires: baseline (T1) and 3 months later (T2). Upon return of their T2 questionnaire, participants are then invited to participate in a dyadic, semi-structured exit interview to further assess acceptability. Data are also collected through the local recruitment logs (covering all steps up to consent), the overall study log (follow-up of enrolled and randomized dyads), and website tracker information.

#### Eligibility screening interview (T0)

A checklist was developed to ensure patients are eligible. Patients must confirm that they are interested in the study, have received (within the last 24 months) or are planning to receive the eligible prostate cancer treatments previously described, that they have a caregiver, and that they have access to the internet. Caregivers must confirm that they are interested and that they have not been diagnosed with cancer themselves in the last year. Reasons for refusal or ineligibility are recorded in the local recruitment logs.

#### Baseline (T1) questionnaire

The online baseline (T1) questionnaire is available in French and English and is completed online via SimpleSurvey by patients and caregivers (separately). The baseline questionnaire includes the following self-administered questionnaires to capture the primary and secondary outcomes of interest. Table 3 includes a summary of the Cronbach’s alpha for each scale.

**Table 3 Tab3:** Cronbach’s alpha’s for measures to be used

Measures	Cronbach’s alpha^a^ measure of reliability
**Physical and emotional outcome measures**	
Medical Outcome Survey (MOS) Short-Form (SF-12) [57]	
Physical Component Summary (PCS)	α = 0.82 [60]
Mental Component Summary (MCS)	α = 0.75 [60]
Hospital Anxiety and Depression Scale (HADS) [42]	α = 0.68–0.93 [62]
Perceived Stress Scale (PSS) [68]	α = 0.75–0.89 [69]
